#### Protocol amendments

The sponsor will treat any protocol amendments according to European guideline "Detailed guidance for the request for authorisation of a clinical trial on a medicinal product for human use to the competent authorities, notification of substantial amendments and declaration of the end of the trial". The regulatory authorities will be notified about substantial amendments and these amendments must be approved before being implemented.

## 9 Assessment of Safety

### 1. Averse events (AE)

Note that the term IMP refers to the pandemic viral A/H5N1 influenza vaccine in this study.

#### Definitions

#### Adverse events

An AE is any untoward medical occurrence in a patient or subject which does not necessarily have a causal relationship with a medical treatment. This includes any noxious, pathological or unintended change in anatomical, physiological, or metabolic functions as indicated by physical signs, symptoms and/or laboratory-detected changes. These might occur in any phase of the clinical study whether associated with or related to the IMP or not. This includes also exacerbations of pre-existing conditions or events, intercurrent illnesses, or vaccine- or drug interactions. Anticipated day-to-day fluctuations of pre-existing conditions that do not represent a clinically significant exacerbation are not considered AEs. Discrete episodes of chronic conditions occurring during a study period should be reported as AE in order to assess changes in frequency or severity.

#### Serious adverse events (SAE)

SAEs are a subset of AEs. A SAE is defined as any untoward medical occurrence or effect at any dose that

- results in death
- is **life-threatening**: i.e. the subject was at risk of death at the time of the event; it does not refer to an event which hypothetically might have caused death if it were more severe
- results in persistent or significant **disability/incapacity**: i.e. results in a substantial disruption of the subject's ability to carry out normal life functions.

- requires in-patient **hospitalisation** or prolongation of existing hospitalisation: i.e. the subject is detained (usually at least an overnight stay) at the hospital or emergency ward for treatment that would not have been appropriate in the physician's office or in an out-patient setting. Hospitalisation for either elective surgery related to a pre-existing condition which did not increase in severity or frequency following initiation of the study or for routine clinical procedures (including hospitalisation for "social" reasons) that are not the result of an AE are **not** considered as SAEs

 A procedure which may take place during the study period and should not interfere with the IMP administration or any of the ongoing protocol-specific procedures.

- is a **congenital anomaly or birth defect** in the offspring of a study subject

- is an **important medical event** that may jeopardise the subject or may require intervention to prevent one of the other outcomes listed above: e.g. interventions such as intensive treatment in an emergency room or at home for allergic bronchospasm; blood dyscrasias or convulsions that do not result in hospitalization, or development of drug dependency or drug abuse. Based on medical and scientific judgment, these events should usually be considered serious

Although **not** considered as SAE, cancer should be reported in the same way as SAEs.

Note: If anything untoward is reported during an elective procedure, that occurrence must be reported as an AE, either serious or non-serious according to the criteria defined above. When in doubt as to whether hospitalisation occurred or was necessary, the AE should be considered serious.

Surveillance, reporting, and documentation of adverse events

The recording of AEs is an essential part of study documentation. The clinical investigator is responsible for documenting all AEs as set out in the following sections.

Documentation of solicited adverse events

Solicited AEs are precisely defined events that the subjects are specifically asked about and which are documented by the subjects in the adverse event form. This form will be the source document and will be added into the CRF.

The following local AEs at the IMP injection site (injections site reactions) will be documented in the Adverse Event Form:

- Pain
- Erythema
- Ecchymosis
- Induration
- Itching
- Swelling

The following solicited systemic AEs will be documented in the adverse event form and transcribed by the investigator into the CRF:

- Body temperature (oral)  $\geq 38^{\circ}\text{C}$
- Malaise
- Shivering
- Fatigue
- Headache

- Sweating
- Myalgia
- Arthralgia
- Diarrhoea
- Respiratory symptoms

An Adverse Event Form will be issued to all subjects instructing them to record their daily local and systemic adverse events for as long as symptoms persist. The subjects will provide information on the presence or absence of solicited local and systemic adverse events. The use of antipyretic/relief medication and any changes in medication will also be recorded. Subjects will score the severity of symptoms as follows:

Blank – no adverse symptoms

1 -symptom occurred but not severe enough to cause inconvenience

2 -symptom occurred severe enough to interfere with daily activities but required minimal or no medical intervention

3-symptom occurred severe enough to markedly interfere with daily activities; required medical consultation

At each visit, all AEs, either observed by the clinical investigator or his nominee or reported by the subjects spontaneously or in response to a direct question will be evaluated by the investigator. As a consistent method to find out about adverse events, the investigator should use a non-leading question, such as:

"Have you felt different since receiving the vaccine or since the previous visit?"

The subjects will be instructed to contact the clinical investigator immediately should they experience any signs or symptoms they perceive as serious during the period extending from the first study-specific procedure up to and including 6 months (minimum 180 days) after the last administration of the IMP.

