#### Study Contact for SAE Reporting:

Pharmacovigilance Department, Crucell Biotech Ltd.

[contact]

[contact]

Outside office hours:

[contact]

E-mail: [[contact]](mailto:[contact])

The completed SAE Report Form should detail all relevant aspects of the SAE, all actions taken by the investigator, the causality, and the outcome of the event. Any new information obtained regarding the SAE must be reported immediately. The SAE Report Forms should be used for documentation of the SAE, any actions taken, the outcome, and for follow-up reports. When applicable, hospital case records and autopsy reports should be obtained by the investigator and forwarded to the Study Contact for SAE Reporting.

The investigator must report SAEs to the appropriate Ethics Committee, if requested by the committee, and/or according to local legal requirements.

Causality of all other AEs should be assessed by the investigator based on the following:

- In your opinion, is there a reasonable possibility that the AE was caused by the IMP?
- Related** there is suspicion that there is a relationship between IMP and AE (without determining the extent of probability); there is a reasonable possibility that the IMP contributed to the AE
- Unrelated** there is no suspicion that there is a relationship between IMP and AE; there are other more likely causes and administration of the IMP is not suspected to have contributed to the AE

Severity of adverse events

The severity of unsolicited AEs will be graded on a 3-point scale as follows:

| Grade        | Definition                                                                                                                                                                               |
|--------------|------------------------------------------------------------------------------------------------------------------------------------------------------------------------------------------|
| 1 (mild)     | Discomfort noted, but no disruption of normal daily activity; slightly bothersome; relieved with or without symptomatic treatment.                                                       |
| 2 (moderate) | Discomfort sufficient to reduce or affect normal daily activity to some degree; bothersome; interferes with normal daily activities; only partially relieved with symptomatic treatment. |

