## SKJEMA FOR EGENRAPPORTERING AV BIVIRKNINGER/REAKSJONER ETTER INFLUENSAVAKSINASJON MED H5N1 VAKSINE

MERK AV I DE RUBRIKKENE SOM PASSER. Grader fra 1-3

1= Svake/ ubetydelige symptomer som ikke gir særlige plager.

2= Symptomer som er så besværlige at de påvirker den daglige aktiviteten, men som ikke krever legetilsyn.

3= Sterke eller vedvarende symptomer som i høy grad påvirker den daglige aktiviteten, eller som krever legetilsyn.

Tom rubrikk betyr "intet å melde". DET ER PÅ BAKSIDEN AV SKJEMAET. Reaksjoner som ikke er nevnt i tabellen: Bruk kommentarfeltet. Angi også i samme kommentarfelt om du har tatt noen medisiner som en følge av reaksjonene, og i så fall hvilke medisiner.

Ved akutt legebehov, se telefonliste på baksiden av skjemaet. Ved bruk av annen lege: Meld fra om at du er med i denne studien.

Skjemaet bringes med til klinikken og vises legen ved hvert fram møte (dagene skravert på skjemaet).

| Dag etter vaksinasjon | Lokale symptomer på injeksjonsted |         |        |                     |          | Generelle symptomer     |                       |           |          |          |        |            |              | Andre hendelser |                                    |       |
|-----------------------|-----------------------------------|---------|--------|---------------------|----------|-------------------------|-----------------------|-----------|----------|----------|--------|------------|--------------|-----------------|------------------------------------|-------|
|                       | Rødhet                            | Hevelse | Smerte | Liten blodutredelse | Hard hud | Feber >38°C (angi temp) | Uvel (beskriv under ) | Skjelving | Tretthet | Hodepine | Svette | Muskelverk | Ledd-smerter |                 | Luftveis-symptomer (beskriv under) | Diaré |
| 0                     |                                   |         |        |                     |          |                         |                       |           |          |          |        |            |              |                 |                                    |       |
| 1                     |                                   |         |        |                     |          |                         |                       |           |          |          |        |            |              |                 |                                    |       |

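### The solicited severity scale gives no grade to a bothersome symptom that leaves daily activity unaffected, and records no extent for visible local signs, which blurs severity comparisons between groups

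*Protocol*

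**What the plan says.** Section 9, Documentation of solicited adverse events, has subjects score each solicited symptom. A blank means none. The lowest grade is worded "1 -symptom occurred but not severe enough to cause inconvenience", so it rests on the absence of any inconvenience. The middle grade changes the criterion to an effect on activity and reads "2 -symptom occurred severe enough to interfere with daily activities but required minimal or no medical intervention". The highest grade, 3, asks for marked interference and, after a semicolon, for a medical consultation.

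The list has six local items: pain, erythema, ecchymosis, induration, itching and swelling. Of the Adverse Event Form the section says: "This form will be the source document and will be added into the CRF".

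The form in the appendix words the grades differently. Its grade 1 reads "1= Svake/ ubetydelige symptomer som ikke gir særlige plager", that is, weak or insignificant symptoms that give no particular trouble. Its grade 2 is trouble great enough to affect daily activity without needing a doctor. Its grade 3 is strong or persistent symptoms that greatly affect activity or need a doctor. It has five local columns (redness, swelling, pain, small bruise, hard skin) and none for itching. It asks for the temperature as a value but for no size of any local sign.

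Unsolicited events have their own scale under Severity of adverse events, where grade 1 is "Discomfort noted, but no disruption of normal daily activity; slightly bothersome; relieved with or without symptomatic treatment".

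The section on solicited events also provides for other data. Presence or absence of each solicited event is collected, subjects are to "record their daily local and systemic adverse events for as long as symptoms persist", and relief medication is noted.

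**The concern.** Local and systemic adverse events and tolerability are the primary endpoints (section 5, item 1), and comparative reactogenicity by dose is a planned publication (section 16). The background on inactivated influenza vaccine says mild local reactions often occur in more than half of healthy adults and rarely interfere with normal activities. The expected reactions therefore lie close to the boundary between grades 1 and 2, where the wording leaves a gap.

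A subject in the gap has to pick a grade without a rule. The trial is open and subjects score themselves, so that pick may be influenced by knowing the dose or that the vaccine contains adjuvant. For the four visible or palpable signs, a small and a large reaction get the same grade if neither affects the subject. Neither loss can be recovered by a later analysis, because the information is never collected.

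**Working it through.** The protocol gives no figure for this point, so there is none to reproduce. The check compares the three scales and then illustrates size under assumed rates.

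**1. Test cases against the three scales**

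| Symptom | Section 9, solicited | Norwegian form | Section 9, unsolicited |
|---|---|---|---|
| Present, not bothersome | 1 | 1 | 1 |
| Slightly bothersome, activity unaffected | none | 1, on a fair reading | 1 |
| Clearly bothersome, activity unaffected | none | none | none |
| Bothersome, activity affected, no doctor needed | 2 | 2 | 2 |
| Marked interference, no doctor consulted | 2 or 3, depending on the semicolon | 3 | 3, if its other clauses are met |

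The second row shows the gap in the protocol text and the different treatment elsewhere. The third row shows that the form does not close the gap. It also shows that the unsolicited wording is no ready replacement: its grade 1 is slightly bothersome without disruption, while its grade 2 is bothersome with interference. The last row shows the grade 3 difference: a semicolon in the protocol, *eller* (or) on the form.

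**2. Local items.** Section 9 lists six, the form has five, and itching is the one missing. Four of the five (redness, swelling, bruise, hard skin) are visible or palpable signs, and neither section 9 nor the form asks for their extent.

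**3. Size, if the gap is scored alike in both groups.** Inputs: 15 per group (section 10). Assumptions, not document figures: two-sided level 0.05; true rates of grade 2 or above of 10% and 40%; a further share g of each group with a gap symptom; a fraction u of those scored 2. The recorded rate is p + g × u. Power is the sum of Bin(x; 15, p1) × Bin(y; 15, p2) over all (x, y) with Fisher exact p ≤ 0.05.

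| g | u = 0 | u = 0.5 | u = 1 |
|---|---|---|---|
| 10% | 0.325 | 0.275 (15% vs 45%) | 0.246 (20% vs 50%) |
| 20% | 0.325 | 0.246 (20% vs 50%) | 0.227 (30% vs 60%) |
| 30% | 0.325 | 0.232 (25% vs 55%) | 0.227 (40% vs 70%) |

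The 30-point difference is kept, but both rates move towards the middle of the scale, where the variance is larger.

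**4. Size, if scoring depends on group.** Suppose two groups have identical experience, and gap symptoms are all scored 1 in one group and all scored 2 in the other. The apparent difference is then g: 0.10 × 15 = 1.5, 0.20 × 15 = 3 and 0.30 × 15 = 4.5 subjects on average. These are the extremes for each assumed g.

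**5. What the gap does not touch.** Any-grade occurrence does not use the boundary. Under assumed rates of 50% vs 90%, Fisher power is 0.54; for 30% vs 80% it is 0.68. Group size is the larger limit: 80% power needs about 10% vs 64%, or 20% vs 76%.

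**The case against.** A reader might infer that the scale cannot separate reactogenicity between dose groups. The protocol does not support that. Presence or absence, daily duration, temperature and relief medication are all recorded and do not depend on the boundary between grades 1 and 2. With 15 per group, sample size limits the comparison more than the wording does. This part of the objection stands.

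It is also fair that subjects score from the form, whose looser grade 1 takes in the mildly sore arm. That stands for slight trouble, but not for clear trouble that leaves activity unaffected. Subjects are instructed in scoring, forms are reviewed at visits and there is a comment field. These safeguards help, but they give no rule for the unplaced case.

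The unsolicited scale covers a different list, and the solicited list is the same in all four groups, so having two scales does not by itself create a difference between groups. This stands. Itching, however, is solicited in section 9 and has no column on the form, so it could end up under either scale.

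It would be wrong to say that visible signs are graded only by inconvenience: grades 2 and 3 use interference and medical need. Nor does the protocol promise a diameter, so its absence contradicts nothing and measuring it is a design recommendation.

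**Conclusion.** The point holds in a limited form. The solicited scale in section 9 is not exhaustive between grades 1 and 2, the form only narrows the gap, and the protocol's scales differ in grade 1 and grade 3 wording. Four of the form's five local columns are scored only by effect on the subject. The consequence is blurred severity data for the primary endpoint, with possible group-dependent scoring because the trial is open. It is not a failure of the safety comparison as a whole.

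Under the assumed rates, power on grade 2 or above falls from 0.33 to between 0.23 and 0.28 when half or all of the gap symptoms are scored 2. Group-dependent scoring could shift 1.5 to 4.5 of 15 subjects on average at most. These figures rest on assumed gap shares of 10% to 30%; the documents give no rate for such symptoms. They also assume that nobody with a symptom leaves the cell blank, which the form says means nothing to report. The protocol claims no powered comparison, so the figures show scale only. The change is worth making because it is cheap and the lost information cannot be recovered later.

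**What to change.** - Use one wording in section 9 and on the Norwegian form, with a single cut. Grade 1: symptom present, bothersome or not, without interference with daily activities. Grade 2: symptom interferes with daily activities. Do not import the unsolicited wording as it stands, since it leaves a similar space.
- Reconcile the grade 3 wording, so that protocol and form say the same about how marked interference and medical consultation combine.
- Reconcile the itching item, which section 9 solicits and the form omits.
- Add a separate millimetre field for the largest diameter of redness, swelling, bruising and induration. It should not share the grade cell, where an entry of 3 could be a grade or a size. Have staff record the same measurement at the existing 45-minute check and day 3 visit after each dose.

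Cost: a short amendment to section 9, a reprinted form and 60 rulers, one per subject. The drawbacks are slightly more diary effort each day and grades less directly comparable with any earlier study that used the old scale.

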#### Documentation of adverse events

Any AE occurring within 3 weeks (minimum 17 days) following vaccination will be recorded on the AE Page of the CRF, irrespective of its severity or potential relationship to the IMP.

Any SAE brought to the attention of the investigator from study start up to 6 months (at least 180 days) after vaccination of that subject will be recorded. AEs not previously documented in the adverse event form will be recorded in the AE page of the CRF. AEs should be documented in terms of signs and symptoms observed by the investigator or reported by subjects. Whenever

possible, a medical diagnosis should be made. The nature of each event, date and (where appropriate) time of onset, outcome, severity and causal relationship should be established. Details of any symptomatic/corrective treatment should be recorded on the appropriate page of the CRF.

Hospitalisation for routine clinical procedures (including hospitalisation for "social" reasons) that are not the result of an AE are not considered AEs but will be recorded on the AE page of the CRF. The same applies for hospitalisation for elective procedures related to a pre-existing condition that did not increase in severity or frequency during the study. If hospitalisation was planned before first administration of the IMP, it will be documented in the Medical History Page of the CRF (see below).

The following events will be documented in the Medical History Page of the CRF:

- AEs which occur after informed consent was obtained, but before the first IMP administration
- Pre-existing conditions or signs and/or symptoms present in a subject before study start. This includes conditions which were not recognized at study entry but later during the study period
- Hospitalisation arising from a pre-existing condition and planned before the first administration of the IMP

#### Reporting of serious adverse events

All SAEs must be reported immediately by the investigator without filtration, independent of their association or causal relation to the IMP. The investigator must report all SAEs within 1 calendar day of becoming aware of the event by telephone, fax or e-mail (if appropriate) to the Study Contact for SAE Reporting as described below.

The initial notification should include all known information regarding the SAE (which may be minimal, but should include sufficient information to permit identification of the reporter, the subject, the IMP, the SAE, and the date of onset of the SAE). The investigator should not wait for additional information to fully document the event before notifying the Study Contact for SAE Reporting. A SAE Report Form should be filled out and sent to the Study Contact for SAE Reporting within 1 day of becoming aware of the event. The initial notification sent by the investigator will be confirmed by an acknowledgement letter. The initial report should then be followed by submission of a completed SAE Report Form provided by the sponsor as soon as possible but at latest within 3 calendar days of the initial report.

By definition, all solicited local AEs occurring at the application site (i.e. all solicited local reactions) will be considered related to the IMP-administration (injection site reactions).

administration of the IMP

- The event has been temporally associated with IMP-administration or reproduced on re-product and/or formulation
- The event has often been reported in literature for similar types of medicinal products
- A reaction of a similar nature has been previously observed with this type of medicinal

determined by how well the event can be understood in terms of one or more of the following:

To which degree of certainty an AE can be attributed to administration of the IMP or to alternative causes (e.g. natural history of the underlying diseases, concomitant therapy) will be serious adverse events.

Every effort should be made by the investigator to explain any AE and assess its potential causal relationship to administration of the IMP. This applies to all AEs, i.e. to both non-serious and

Causality of adverse events

The reporting obligations for SUSARs will be fulfilled as required by the applicable law.

